## **METHODS**

### ***Study design***

Single-center, single-arm experimental study conducted on a cohort of subjects attending the A. Gemelli IRCCS University Hospital in Rome (Italy), enrolled at the outpatient clinics of the Cardiology Department.

### ***Population***

Participants will be selected from among subjects attending the A. Gemelli IRCCS University Hospital in Rome (Italy).

Recruitment will be carried out at the cardiovascular prevention clinics, in collaboration with the Cardiology Unit.

### ***Duration of the study***

7 months

### ***Inclusion criteria***

- Traditional cardiovascular risk, measured using SCORE 2 (Low risk (< 2.5%); Moderate risk (between 2.5% and 5%); High risk (between 5% and 10%) or with SCORE 2-OP (Moderate risk (< 7.5%); High risk (between 7.5% and 15%))
- Availability of blood tests within the previous 6 months
- Subjects aged  $\geq 40$  years.

### ***Exclusion criteria***

- Very high cardiovascular risk measured using SCORE 2 (very high risk > 10%) or SCORE 2-OP (very high risk > 15%)
- Diabetes
- Familial hypercholesterolemia
- Previous cardiovascular events

### ***Procedures***

The study includes an initial enrollment phase (T0) for subjects attending the A. Gemelli IRCCS University Hospital in Rome (Italy).

Subjects who agree to participate in the PHC study will be given the specific informed consent form for this study and will undergo a baseline assessment, including questionnaires to be completed and blood sampling for PRS assessment. The results of the will be communicated in an informative visit about one month later (T1). Finally, subjects will be re-evaluated six months (T2) after the informative visit to reassess their lifestyle. Specifically, at the time of enrollment (T0), all participants will sign an informed consent form and undergo a comprehensive assessment:

- They will complete the LE'8 questionnaire, which includes information on socioeconomic status and lifestyle, in particular smoking status, alcohol consumption, dietary patterns, sleep patterns,

and physical activity.

- they will undergo a complete medical examination to collect biometric data (such as BMI, body circumference), heart rate, and blood pressure.
- Patients will provide blood tests performed independently in the last six months, reporting lipid profile values (total cholesterol, HDL and LDL cholesterol, triglycerides), glycemic or glycated hemoglobin, to calculate the SCORE-2 / SCORE 2-OP score. If these tests are missing or too old, in order to avoid excluding the patient, a blood sample will be collected to determine the above-mentioned values.
- Blood sample for analysis and calculation of the genetic predisposition profile to developing cardiovascular disease, using the Polygenic Risk Score.
- Biological samples (whole blood) will be stored.

A lifestyle score will be calculated for each participant based on the LE8 score.

During the informative telematic visit (T1), the lifestyle score will be explained. Participants will receive personalized written preventive advice to reduce unhealthy behaviors and modify their lifestyle. The PRS results will also be disclosed to all participants and the risk profile category will be provided, with all relevant information. At the six-month follow-up from T1 (T2), participants will receive a complete final assessment, as at T0, which includes the submission of the lifestyle questionnaire and the recalculation of the lifestyle category, as well as biometric tests (weight, BMI, body circumferences, heart rate, blood pressure). At the same time, for a new SCORE2/SCORE2 OP assignment, a blood sample will be taken for the re-evaluation of the lipid profile (total cholesterol, HDL, LDL), blood glucose/glycated hemoglobin. In addition, lipoprotein (a) and troponin I will be measured.

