## **ENDPOINTS**

### ***Primary endpoint***

- Pre-post change in lifestyle score, measured using Life Essentials' 8, at baseline and at final follow-up [17,18,19,20]
- Changes in cardiovascular risk profile assessed using SCORE2 / SCORE2 OP

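### Baseline lipids and glycaemia may be up to six months old and from an unspecified laboratory, while follow-up values come from a fresh study sample, so the laboratory parts of both primary endpoints may not be like for like

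*Protocol*

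**What the plan says.** Both primary endpoints are changes from baseline. The first is given as "Pre-post change in lifestyle score, measured using Life Essentials' 8, at baseline and at final follow-up" and the second is change in SCORE2/SCORE2-OP (Protocol, Primary endpoint). The study has one arm (Study design).

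The laboratory values behind these scores are obtained differently at the two visits (Procedures):

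- **T0, default:** "Patients will provide blood tests performed independently in the last six months, reporting lipid profile values". The glycaemic item and the purpose of the panel are worded "glycemic or glycated hemoglobin, to calculate the SCORE-2 / SCORE 2-OP score".
- **T0, exception:** "If these tests are missing or too old, in order to avoid excluding the patient, a blood sample will be collected".
- **T2:** "a blood sample will be taken for the re-evaluation of the lipid profile (total cholesterol, HDL, LDL), blood glucose/glycated hemoglobin".

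The Questionnaire section lists cholesterol and blood sugar, with BMI and blood pressure, as the health factors in LE8.

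The Inclusion criteria list "Availability of blood tests within the previous 6 months" as a requirement, which the T0 exception waives.

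Every participant has blood taken at T0 for another purpose: "Blood sample for analysis and calculation of the genetic predisposition profile to developing cardiovascular disease, using the Polygenic Risk Score".

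The Protocol does not require the same laboratory or the same glycaemic analyte at both visits.

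**The concern.** In a single-arm pre-post study the estimated effect is the post value minus the pre value. No comparator exists to cancel a difference in how, where or when the two were measured. Here the default baseline for the laboratory items is a value the participant brings, from an unnamed laboratory and dated at any point in the previous six months. The follow-up value is always a fresh study sample.

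Two kinds of spurious change can enter:

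1. **Real change that precedes the study.** A shift in lipids or glucose between the old test and T0 is booked as change after disclosure of the PRS, although it came before enrolment. This can happen even if every test was done in the same laboratory.
2. **Measurement difference.** If the T0 sources read higher or lower on average than the T2 laboratory, or if a participant has glucose at one visit and glycated haemoglobin at the other, the difference becomes part of the effect.

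Each composite score also mixes baseline dates, because the questionnaire items, BMI and blood pressure are recorded at T0 itself. This is a data-collection rule. Analysis cannot recover a T0 value that was never measured.

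**Working it through.** **1. The plan's own figures (Sample calculation).** 650 × 0.70 = 455 participants and 455 × 0.80 = 364 completers; both reproduce. For a mean LE8 change of 3 with SD 2, the standard error is 2/√364 = 0.105 and 3/0.105 ≈ 28.6. With two-sided alpha 0.05 (assumed, as none is stated), power is effectively 100%, in line with the stated figure of more than 90%. The sample size is not in dispute here.

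**2. Which inputs are affected.**

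| Item | T0 source | T2 source |
|---|---|---|
| Smoking, alcohol, activity, sleep, diet | Study questionnaire at T0 | Study questionnaire at T2 |
| BMI, blood pressure | Study examination at T0 | Study examination at T2 |
| Lipids | Participant's own test, up to 6 months old; study sample only if missing or too old | Fresh study sample |
| Glucose or glycated haemoglobin | As for lipids; either one accepted | Fresh study sample; both are named, separated by a slash |

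Only the last two rows change source. They supply two LE8 components and the lipid inputs of SCORE2/SCORE2-OP.

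**3. Interval from baseline value to T2.** Interval = age of test at T0 + T0 to T1 (about 1 month) + T1 to T2 (6 months).

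- Fresh T0 sample: 0 + 1 + 6 = about 7 months.
- Six-month-old test: 6 + 1 + 6 = about 13 months.

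The laboratory interval therefore varies between participants from about 7 to about 13 months. It is about 7 months for all other items.

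**4. Illustration of how a shift carries through to LE8.** The Protocol does not state the component weights. Assume LE8 is the unweighted mean of eight components, each on 0 to 100, and that every participant's two laboratory components shift by b points in the same direction. The shift in LE8 is 2b/8 = b/4.

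| b (assumed) | LE8 shift, b/4 | Share of the 3-point target |
|---|---|---|
| 1 | 0.25 | 8% |
| 5 | 1.25 | 42% |
| 10 | 2.50 | 83% |
| 12 | 3.00 | 100% |

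The Questionnaire section also lists alcohol, which makes nine items. With nine equal weights the shift is 2b/9, so b = 5 gives 1.11 and b = 10 gives 2.22. If only a fraction f of participants is affected, the shift is f × b/4; with f = 0.5 and b = 5 it is 0.5 × 1.25 = 0.625. Neither b nor f can be obtained from the Protocol.

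**5. How small a shift the test would pick up.** With 364 completers and two-sided alpha 0.05, the observed mean change is significant above 1.96 × SD/√364. That is 0.21 points at the Protocol's SD of 2, and 1.03 points at an assumed SD of 10. With no true change, a shift of b = 1 in everyone (0.25 LE8 points) would give a significant result with probability 66% at SD 2 and 8% at SD 10. For b = 5 (1.25 points) the figures are about 100% and 66%. These numbers describe the sensitivity of the test. They are not evidence that a shift exists.

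**The case against.** In favour of the plan, the following can fairly be said.

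- **A mean bias is not shown.** A change of source biases the mean only if the T0 sources read differently on average from the T2 laboratory; otherwise it mainly adds noise. The Protocol gives no size or direction. This stands, and it is why the table above is an illustration only.
- **The laboratory is not known to be external.** A reader might infer that baseline values come from outside laboratories. The Protocol says only that the tests were done independently. Participants attend this hospital, and the Sample calculation section says the study is offered to its employees, so some tests may be in-house. This stands, but it does not remove the timing problem.
- **Some baselines are fresh.** Participants without usable tests get a T0 study sample, so the baseline is a mixture and 13 months is the extreme. This also stands.
- **The analyte may not change.** The slash in the T2 wording may mean that both glucose and glycated haemoglobin are measured. Only the T0 wording clearly accepts either. A change of analyte is therefore possible but not established.
- **Covariates belong in the statistical analysis plan.** The Statistical Analysis section already foresees adjusted mixed models, and the covariate list may be given elsewhere. That is fair for the choice of covariates, but adjustment does not replace a baseline that was not collected.
- **The inclusion criterion is an editorial matter.** Procedures state the exception and its reason. This is right: the two sections need reconciling, but the mismatch adds nothing to the measurement argument.

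**Conclusion.** The concern holds for the laboratory-based parts of both primary endpoints: cholesterol and blood sugar in LE8, and lipids in SCORE2/SCORE2-OP. As written, these parts may differ between pre and post in source and, for glycaemia, in analyte. They span about 7 to 13 months where the other items span about 7. Without a comparator, any change between the old test and T0, or any net laboratory difference, is counted as change after disclosure.

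The size and direction are unknown. The b/4 relation rests on eight equal weights and on a uniform shift in both components for everyone; a partial or mixed shift would be smaller.

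A reader might go further and conclude that both primary endpoints as a whole compare non-comparable measurements, or that a systematic bias is built in. The Protocol does not support that. Most LE8 items, and blood pressure, are collected by the study at both visits, and nothing shows that the T0 sources read consistently high or low. The weakness is real but partial, and cheap to remove. It should be fixed, but it is not shown to invalidate either endpoint.

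**What to change.** Change the T0 procedure so that every participant has the same lipid and glycaemia panel taken at the venepuncture already done for the PRS. Add a tube if needed, because the Protocol does not show that the blood drawn for genotyping and storage is suitable for this panel. Specify the same laboratory and the same analyte (glucose or glycated haemoglobin) at T0 and T2, and state that only these T0 values are the baseline for LE8 and SCORE2/SCORE2-OP. Keep older participant-supplied tests for pre-screening only. Reconcile the inclusion criterion on available tests with the exception in Procedures, and say which value decides eligibility, since SCORE2 is itself an entry criterion.

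The cost is one routine panel for up to about 455 people, fewer in net terms because those without recent tests already have it under the present rule, plus a short protocol edit. No extra visit is needed.

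If a panel for everyone is refused, adjust the models for test source and test-to-T0 interval, and run a sensitivity analysis limited to participants with a study-laboratory sample at T0. This is weaker. Under the present rule that subgroup consists of people who lacked recent tests, so it may not represent the rest.

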## DATA COLLECTION, RECORDING, AND STATISTICAL ANALYSIS

### *Questionnaire*

The study questionnaire is divided into several sections.

The lifestyle questionnaire (Life's Essential 8) will be administered at T0 and T2, and after completion, will provide a lifestyle score that will classify the patient into one of three categories (favorable, intermediate, unfavorable). The questionnaire has been validated on the European population and has already been used in several clinical studies. Its scale ranges from 0 to 100 [20].

It is divided into several sections, structured as follows:

**General lifestyle:** Smoking habits, alcohol consumption, physical activity, and amount of sleep

**Diet:** Types of foods included in one's diet

**Health factors:** BMI, cholesterol, blood pressure, and blood sugar

Questionnaire on personal and family history, socioeconomic and professional status, and demographic information, administered at T0. Questionnaire on the acceptability of the intervention to doctors and patients, administered at T2. Questionnaire on values and preferences regarding the use of new technologies [21], administered at T2. FACToR questionnaire, a revised version of the MICRA questionnaire, to assess the reaction to genetic testing [22][23], administered at T2.

At both T0 and T2, a questionnaire will be administered to assess anxiety levels (GAD-7) [24] and work status (Work Ability Index) [25].

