### ***Primary objective***

- To evaluate the effectiveness of communicating the Polygenic Risk Score in modifying participants' lifestyle.

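### The primary 'lifestyle score' is about half health factors that treatment can also move, and the protocol names no medication recording to tell the two apart

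*Protocol*

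**What the plan says.** All references are to the protocol; no statistical analysis plan was available.

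- **Primary objective:** "To evaluate the effectiveness of communicating the Polygenic Risk Score in modifying participants' lifestyle".
- **Primary endpoint:** "Pre-post change in lifestyle score" by LE8 from baseline to final follow-up, and "Changes in cardiovascular risk profile assessed using SCORE2 / SCORE2 OP".
- **Questionnaire:** the LE8 content is given as general lifestyle ("Smoking habits, alcohol consumption, physical activity, and amount of sleep"), diet, and health factors ("BMI, cholesterol, blood pressure, and blood sugar"). Of the score it says: "Its scale ranges from 0 to 100".
- **Procedures:** the lifestyle score is derived from LE8. Here, however, the LE8 questionnaire is described as covering socioeconomic status and behaviours, alcohol included, without the health factors.
- **Secondary endpoints:** smoking, eating pattern, alcohol and physical activity appear as counts of participants who changed. Sleep does not appear.
- **Study design, Population, Inclusion and Exclusion criteria:** one arm. "Recruitment will be carried out at the cardiovascular prevention clinics". Eligibility runs up to the high category of SCORE2 or SCORE2-OP. Very high risk, diabetes, familial hypercholesterolemia and previous events are excluded; current or new drug treatment is not.
- **Medication:** no medication item is named at T0 or T2. Personal history is taken at T0 only.

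**The concern.** The question is about behaviour, while the measure mixes behaviours with clinical measurements. Cholesterol, blood pressure and blood sugar can improve because treatment was started or changed. That is a plausible event among people seen at prevention clinics, some of them at high risk, who are given a genetic risk category at T1 and remeasured six months later. With no control arm, nothing in the design absorbs such a change, so it would count as a gain in the lifestyle score. SCORE2/SCORE2-OP, the other primary endpoint, has the same weakness because it is recalculated from the new blood values.

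The baseline blood tests widen the window. They may be up to six months old at T0, T1 follows about one month later, and T2 six months after that: 6 + 1 + 6 = up to about 13 months between the two blood measurements. A treatment change that preceded disclosure of the genetic result could fall inside that interval.

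The mixture can also work the other way. If the health factors barely move in six months, a real behavioural gain is diluted in the total. At stake is whether the primary result, in either direction, answers the primary objective.

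**Working it through.** **1. The plan's own figure.** From Sample calculation: 650 × 0.70 = 455 and 455 × 0.80 = 364 completers, a 3-point mean change, SD 2. Taking the SD as that of the change and assuming two-sided alpha 0.05 (alpha is not stated):

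power = Φ(3 / (2/√364) − 1.96) = Φ(28.6 − 1.96), about 100%.

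The stated power above 90% is reproduced.

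**2. Share of health factors.** Domains listed under Questionnaire: smoking, alcohol, activity, sleep, diet, BMI, cholesterol, blood pressure, blood sugar = 9.
- Health factors: 4/9 = 44%, or 4/8 = 50% if alcohol is not scored.
- Without BMI, which is less directly moved by drugs: 3/9 = 33%, or 3/8 = 38%.

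**3. What the planned effect means by component.** Assume the total is an equally weighted mean of eight 0-100 components (the protocol gives no scoring rule).
- A 3-point gain is 3 × 8 = 24 component-points.
- With no behaviour change, it needs a mean gain of 24/4 = 6 points on each health factor, or 24/3 = 8 on each of cholesterol, blood pressure and blood sugar.
- With no health-factor change, the four behaviours must gain 24/4 = 6 points each on average to show 3 on the total.
- With nine components the corresponding gains are 27/4 = 6.75 on each of four and 27/3 = 9 on each of three.

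**4. Illustrative treatment-driven shifts.** Shift = share of participants × points gained ÷ 8. The shares and gains are assumptions, not figures from the protocol.

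| Share | Gain | Shift in total | Of planned 3 |
|---|---|---|---|
| 5% | 20 on one component | 0.05 × 20/8 = 0.125 | 4% |
| 10% | 40 on one component | 0.10 × 40/8 = 0.5 | 17% |
| 20% | 40 on each of two | 0.20 × 80/8 = 2.0 | 67% |

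**5. Would such shifts be detected?** The shift with 90% power is (1.96 + 1.28) × SD/√364; the smallest significant observed shift is 1.96 × SD/√364.
- SD 2 (protocol): 0.34 and 0.21 points. The 0.125 shift alone falls below both; 0.5 and 2.0 exceed both.
- SD 10 (assumed, for range): 1.70 and 1.03 points. Only the 2.0 shift exceeds them.

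**6. Is medication captured elsewhere?** Procedures lists examination, biometrics and blood tests at T0. The T2 assessment is described as complete and as at T0, but what it itemises is questionnaire, biometrics and blood tests. The personal-history questionnaire is given at T0 only, so even if it records drugs it would not show a change by T2. The Statistical Analysis section specifies adjusted mixed models and does not mention medication.

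**The case against.** Several counter-arguments have force.

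- **A reader might infer that the score is mostly drug-driven.** It is not: health factors are 44-50% of the listed content and the three more directly drug-movable ones 33-38%. Excluding diabetes weakens the blood-sugar route further. This stands.
- **No treatment change is documented.** The protocol never mentions starting or intensifying drugs, T1 gives lifestyle advice, and groups likely to need treatment changes are excluded. The background describes healthy, low-risk individuals and Sample calculation describes hospital employees, which does not fit the clinic recruitment and high-risk eligibility stated elsewhere. The route is therefore plausible, not shown.
- **The illustrative sizes are chosen inputs.** This stands; the low case is negligible.
- **Behaviour is already examined.** The secondary counts would partly reveal a rise in the total without behaviour change. They omit sleep and do not govern the primary conclusion.
- **Covariates and sub-score reporting often belong in the statistical analysis plan.** This is fair for the model terms. It does not cover data collection, because a later plan cannot recover medication changes that were never recorded. Nor does an unlisted item prove that none is collected, so it would go too far to say the two effects cannot be separated.
- **A behaviour-only primary score would be fully self-reported,** in a single arm that has just been advised to change. This is a real reporting-bias trade-off and a good reason to keep the total.

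**Conclusion.** The point holds in a limited form. The primary objective concerns lifestyle; the score used to judge it is about half health factors; and the protocol names nothing that would distinguish a treatment-driven gain from a behavioural one. As written, the plan could label the former as the latter.

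The size is unknown. Under equal weighting of eight components and assumed shares and gains, the shift runs from about 0.1 to 2.0 points against the planned 3. The 2.0-point case should not be read as an expected bias: the protocol gives no rate of treatment change, and dilution of a real behavioural effect pulls the other way. No net direction of bias is established. The documents also do not support concluding that a positive result would be due to drugs.

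The score's content is itself unsettled, since Procedures and Questionnaire describe LE8 differently and nine domains are listed for a score named after eight. This is worth correcting before enrolment because the remedy is cheap and the missing data may not be recoverable.

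**What to change.** 1. Keep total LE8 as the primary score. Prespecify the behaviour sub-score (diet, physical activity, smoking, sleep) and the health-factor sub-score as required analyses beside it, and state that lifestyle change will be claimed only if the behaviour sub-score supports it.
2. Record lipid-, pressure- and glucose-lowering medication at T0 and T2. Where an older blood test serves as baseline, also note any change since its date.
3. Repeat the LE8 and SCORE2/SCORE2-OP analyses flagging or excluding participants whose medication changed.
4. Reconcile Procedures and Questionnaire on what enters the score and how it is weighted, and say whether alcohol is scored or is only the separate secondary endpoint.

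Cost: protocol wording, one short item at two existing visits, and a little more analysis. The behaviour sub-score is self-reported, so the lifestyle claim will rest partly on reported data; showing the measured sub-score alongside makes that visible. Excluding participants whose medication changed selects on an event after baseline, so that analysis is a sensitivity check and not a replacement for the main one.
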